## Abstract

**Background:**

Microalbuminuria is an independent risk factor for cardiovascular and kidney disease and a predictor of end organ damage, both in the general population and in persons with HIV (PWH). Microalbuminuria is also an important risk factor for mortality in PWH treated with antiretroviral therapy (ART). In the ongoing Renal Risk Reduction (R3) study in Nigeria, we identified a high prevalence of microalbuminuria confirmed by two measurements 4–8 weeks apart in ART-experienced, virologically suppressed PWH. Although Stage 1 or 2 hypertension and exposure to potentially nephrotoxic antiretroviral medications were common in R3 participants, other traditional risk factors for albuminuria and kidney disease, including diabetes, *APOL1* high-risk genotype, and smoking were rare. Co-infection with endemic pathogens may also be significant contributors to albuminuria, but co-infections were not evaluated in the R3 study population.

**Methods:**

In Aim 1, we will cross-sectionally compare the prevalence of albuminuria and established kidney disease risk factors in a cohort of PWH to age- and sex-matched HIV-negative adults presenting for routine care at the Aminu Kano Teaching Hospital in Kano, Nigeria. We will leverage stored specimens from 2500 R3 participants and enroll an additional 500 PLWH recently initiated on ART (≤ 24 months) and 750 age- and sex-matched HIV-negative adults to determine the contribution of HIV, hypertension, and other comorbid medical conditions to prevalent albuminuria. In Aim 2, we will follow a cohort of 1000 HIV-positive, ART-treated and 500 HIV-negative normoalbuminuric adults for 30 months to evaluate the incidence and predictors of albuminuria.

**Discussion:**

The findings from this study will support the development of interventions to prevent or address microalbuminuria in PWH to reduce kidney and cardiovascular morbidity and mortality. Such interventions might include more intensive monitoring and treatment of traditional risk factors, the provision of renin-angiotensin aldosterone system or sodium-glucose cotransporter-2 inhibitors, consideration of changes in ART regimen, and screening and treatment for relevant co-infections.

**Supplementary Information:**

The online version contains supplementary material available at 10.1186/s12879-022-07531-y.

## Background

In some forms of kidney disease, such as diabetic nephropathy, the earliest detectable abnormality is often microalbuminuria. Albuminuria is an independent risk factor for cardiovascular complications and is a predictor of end organ damage including chronic kidney disease (CKD) [1–4]. Even very low levels of albuminuria, assessed as urine albumin/creatinine ratio (uACR), of 10–30 mg/g) have been associated with adverse cardiovascular and kidney events. [5, 6] Microalbuminuria is used in the early detection of disease states characterized by microvascular dysfunction, such as preeclampsia and diabetic nephropathy, as well as medication-induced nephrotoxicity [7, 8]. Micro- and macroalbuminuria are also important risk predictors for mortality in antiretroviral therapy (ART)-treated PWH, likely as a marker for inflammation and endothelial activation [9, 10]. Albuminuria has been associated with decreased CD4 cell counts and higher plasma viral loads in PWH, as well as increased systemic T-cell activation and more rapid progression to AIDS [5, 11, 12].

In recently published data from our NIDDK-funded R3 study [13, 14] among PWH, ages 18–69 years who were on ART for ≥ 6 months, ~ 40% of 2500 enrolled participants had some level of persistent albuminuria. Why is albuminuria so common in this HIV-positive, ART-experienced population? We hypothesized that genetics play an important role, given the high prevalence of *APOL1* renal risk variants in West Africa [13, 14]. However, genotyping in the R3 study revealed lower than anticipated prevalence of the high-risk (HR) *APOL1* genotype (6.2%), which has been associated with kidney disease risk [13]. The high rates of albuminuria observed in the R3 study population likely reflect a mix of both reversible microvascular endothelial injury (inflammation driven) and non-reversible podocyte damage (irreversible and progressive to CKD). The current study is designed to evaluate additional potential contributors to the high observed rates of albuminuria observed in PWH in Nigeria. *APOL1* high risk genotype and traditional risk factors (e.g., hypertension, diabetes, smoking) do not fully explain the high rates of albuminuria in the R3 study population, although hypertension is likely to be a significant contributing factor. In a prior study in Nigeria, adults with high normal blood pressure (BP) (systolic blood pressure [SBP] 130–139 mmHg and/or diastolic blood pressure [DBP] 85–89 mmHg) had higher rates of microalbuminuria (12.9% vs. 4.1%) and cardiovascular disease risk factors than those with optimal BP. Sickle cell disease and sickle cell trait are also common, with sickle cell trait affecting 1 in 12 African Americans and nearly 300 million people worldwide [15–17]. Although sickle cell trait is often considered a benign condition, kidney manifestations may include impaired urinary concentrating ability, hematuria, and papillary necrosis [17–21]. Although the relationship of sickle cell trait to long-term CKD has not been firmly established, prior studies have showed a higher-than-expected prevalence of sickle cell trait among participants with end stage kidney disease (ESKD). [15, 22, 23]

Other factors that may contribute to albuminuria can be broken down into three main categories: i) *direct kidney injury* (i.e., exposure to the ARV medication TDF, which can cause tubulopathy); ii) *immune activation/inflammation* from HIV or specific viral pathogens (e.g.*, Cytomegalovirus* [CMV], hepatitis B or C) and/or other endemic co-infections (e.g., parasitic infestations, tuberculosis); and iii) *environmental factors/exposures* (*i.e*., traditional medications, heavy metals, etc.). This study will include an in-depth evaluation of direct kidney injury and immune activation/inflammation. Depending on results, future studies may evaluate potential environmental exposures.

Because R3 participants were ART-experienced, with the majority receiving TDF at some point in their course, another important research question is to determine whether albuminuria is *tubular* or *glomerular* in etiology. Tenofovir is an effective ARV medication, widely used in first-line ART regimens [24, 25]. Although data suggest that it is not universally associated with kidney toxicity [26–30], it can be associated with renal tubular dysfunction, including Fanconi syndrome [25, 30–33]. This is especially important in our study setting, where the alternative formulation of tenofovir, tenofovir alafenamide (TAF), which has a more favorable bone and kidney toxicity profile, is not routinely available.

Despite improved patient survival with ART [34, 35], non-AIDS defining conditions such as cardiovascular and kidney disease and non-AIDS-defining malignancies are more prevalent among ART-treated HIV-positive than HIV-negative adults [34, 36–39]. While factors such as smoking and ARV-related toxicity explain some of the increased risk for these events [34, 40], excess immune activation, inflammation, and poor immune restoration [34, 41–51] have also been shown to predict disease. Chronic immune activation and inflammation are hallmarks of HIV infection. [34, 51, 52]

A diverse array of plasma biomarkers [53], including indices of T-cell activation [34, 54, 55], soluble tumor necrosis factor receptor I (sTNFR-I), sTNFR-II, and interleukin-6 (IL-6) [52, 56] are elevated in untreated HIV infection and often remain elevated among ART-treated adults who are fully virologically suppressed [34, 37, 47, 57, 58]. Many mechanisms have been proposed to explain this inflammatory state, including the direct effects of HIV replication (specifically viral protein production), HIV-mediated destruction of mucosal barriers with chronic exposure to gut microbial elements, and coinfections (e.g., CMV) [34, 59, 60]. Recent studies have shown that morbidity and/or mortality are associated with serum inflammation biomarkers, including IL-6, fibrinogen, C-reactive protein, soluble CD14 (sCD14), D-dimer, and cystatin C [34, 41, 42, 45, 46, 48, 49, 61]. Tenorio et al. showed that higher levels of IL-6, sTNFR-I, sTNFR-II, D-dimer, and sCD14 at baseline and pre-event time points were associated with non-AIDS-related morbidity or death [34]. These effects were independent of traditional risk factors, other comorbid conditions, age, ART regimen, and ART-associated immunologic recovery [34].

Systemic inflammation in persons with HIV may also occur in the setting of co-infections. For example, inflammation from parasitic infections, including malaria may cause clinical manifestations [62–69]. Parasitic infections can present with a range of glomerular diseases, most commonly membranoproliferative glomerulonephritis, while membranous glomerulopathy, focal segmental glomerulosclerosis (FSGS), and minimal-change disease are also occasionally seen [67, 68]. In West Africa, chronic parasitic infestations such as schistosomiasis (*Schistosoma haematobium and mansoni*), filariasis (*Wuchereria bancrofti*), onchocerciasis (*Onchocerca volvulus*), strongyloidiasis (*Strongyloides stercoralis*), and Loiasis (*Loa loa*) are potential infectious causes of nephrotic and nephritic syndromes [67, 68, 70]. In addition to overt kidney injury, parasitic infections may also promote local or systemic inflammation, as indicated by elevated levels of inflammatory biomarkers [69, 70].

Co-infection with certain viruses, such as CMV and hepatitis B and C, are common among PWH [71]. Among PWH, CMV seropositivity has been associated with persistent CD8 T-cell elevation and increased risk of developing non-AIDS comorbidities, despite long-term ART [72, 73]. CMV-seropositive individuals with and without HIV have increased epithelial gut damage, microbial translocation, and inflammation. However, little is known about the prevalence and impact of CMV in Nigeria. The estimated prevalence of hepatitis B virus (HBV) and hepatitis C virus (HCV) is 7.6% and 1.7%, respectively, among Nigerian adults (15–64 years of age) [74]. Various forms of kidney injury have been described in relation to HBV, including membranous nephropathy, membranoproliferative glomerulonephritis, and polyarteritis nodosa [69, 75]. In addition to these viral co-infections, mycobacterial infections may present with a diverse spectrum of kidney injuries, including post-infectious glomerulonephritis. Co-infection with *M. tuberculosis* (TB)*,* which is endemic in West Africa, particularly among HIV-positive individuals, is also associated with multiple nephropathies including chronic interstitial nephritis and proliferative glomerulonephritis [76].

To better understand the high rates of microalbuminuria in our population, we plan to test the following overarching hypothesis: hypertension (including pre-hypertension), immune activation from co-infections, and cumulative, long-term exposure to potentially nephrotoxic ARV medications contribute to the high rates of persistent microalbuminuria in these ART-experienced adults. To evaluate this overarching hypothesis, we plan the following specific aims, with each aim having its own additional supporting hypothesis or hypotheses:To compare the prevalence of albuminuria and established kidney disease risk factors in a large cohort of PWH to age- and sex-matched HIV-negative adults presenting for routine medical care at the Aminu Kano Teaching Hospital (AKTH) in Kano, Nigeria. ***Hypothesis***: *HIV-negative adults will have lower prevalence of albuminuria, as well as lower prevalence of hypertension and hepatitis B and C co-infection, when compared to PWH.*To determine the role that hypertension and other comorbid medical conditions (e.g., sickle cell trait or disease, immune activation/inflammation from parasitic, viral, and bacterial infections, and exposure to potentially nephrotoxic ARV medications), have on the risk for development of albuminuria. ***Hypotheses***: *a) Participants with hypertension (controlling for age and stage of hypertension) will have significantly higher rates of albuminuria; b) ongoing inflammation, as evidenced by higher levels of traditional and kidney-specific inflammatory biomarkers, will be associated with higher rates of albuminuria; and c) cumulative exposure to TDF significantly contributes to risk of incident albuminuria among PWH.*

## Methods/design

### Aim

The goal of this study is to better understand the factors contributing to the high rates of microalbuminuria observed in virologically suppressed PWH in Nigeria. By establishing an age- and sex-matched HIV-negative cohort and screening both study populations for cofactors including viral (CMV, hepatitis B & C), parasitic, and mycobacterial (TB) coinfections that may lead to immune activation/inflammation, as well as long-term exposure to potentially nephrotoxic ARV medications (particularly TDF) among PWH, we anticipate our study findings to inform the development of specific interventions to address albuminuria and result in reductions of kidney and cardiovascular morbidity and mortality.

### Setting

This study will be conducted in the U.S. President’s Emergency Plan for AIDS Relief (PEPFAR)-funded HIV clinic at AKTH in Kano, a state in northwest Nigeria. Kano is the most populous state in Nigeria and has an HIV prevalence of 1.3% [77]. AKTH is a large tertiary center that provides care for more than 10,000 adult PWH. Potentially eligible study participants for this study will be identified from 2 main clinics located on the grounds of AKTH; (i) the HIV-negative adults will be identified from the General Outpatient Department (OPD) and the (ii) newly enrolled PWH plus the R3 participants called back (Fig. 1) will be identified from the Prof. S.S. Wali Virology Centre. AKTH has longstanding collaborations with Vanderbilt University Medical Center and is the site for multiple clinical trials, primarily funded by the U.S. National Institutes of Health (NIH) and the Bill and Melinda Gates Foundation.

**Fig. 1 Fig1:**
[figure not shown]
Enrollment Chart

### Study design

The study includes 2 specific aims; a cross-sectional Aim (Aim 1) and a longitudinal Aim (Aim 2) (see below and Fig. 1).

### Specific aim 1

#### Study population

The *inclusion criteria* are as follows:18–69 years of ageWilling and able to provide informed consent.

The *exclusion criteria* are:Pregnant (all women with reproductive potential will undergo urine pregnancy testing)Known congenital kidney disease or autoimmune disease (e.g., systemic lupus erythematosus) that can cause albuminuria

#### Study procedures

##### HIV-negative adults

Trained study staff will present the recruitment script at the time of screening. After subjects provide informed consent, HIV-negative participants will be tested for HIV in accordance with existing national standard/policy as follows:Participant will undergo point-of-care (POC) HIV rapid testing (via finger prick)If their POC HIV rapid test is **positive**, the Determine HIV-1/2 assay kit (Abbott Laboratories) with UniGold test (Trinity Biotech) will be used as the confirmatory test. If needed, the HIV-1/2 STAT-PAK Dipstick assay (Chembio Diagnostic Systems will be used as tiebreaker.If their confirmatory HIV testing is **positive**, they are not eligible to continue in the study but will be informed of their status and will receive appropriate counseling by study staff, all of whom have IRB training and extensive HIV counseling experience. They will be referred for care per existing national standards. If the HIV test is **negative**, participants will be asked to complete a brief risk assessment, asking, “*Have you engaged in any high risk (i.e., unprotected intercourse with a person with known HIV or unknown HIV status, *etc*.) one or more times within the prior 4–6 weeks*?” (**NOTE**: those who are currently healthcare workers will also be asked if they have had any needlestick and/or mucous membrane exposures from someone with known HIV-positive or unknown HIV status within the prior 4–6 weeks). Based on responses to the risk assessment question, subjects deemed *high-risk* (answering **yes** to any question), will undergo viral load (VL) testing.ALL consenting subjects with a **negative** POC HIV rapid test at their screening visit, regardless of their responses to the above risk assessment question, will be asked to provide urine specimens at the study clinic (visits 1 and 2) for uACR measurement. They will also have a blood specimen obtained for genetic testing (at visit 2; see Table 1).When VL results are available (in ~ 2–3 weeks), participants will be called back to receive results and counseling to reduce transmission risk or for referral to care if HIV-positive. Screened high-risk individuals having a detectable VL (> 50 copies/mL) are not eligible for the study and will be provided counseling and referral to care, as detailed above.

**Table 1 Tab1:** Procedures for cross-sectional cohort of age- and sex-matched HIV-negative participants (n = 750), plus the newly enrolled HIV-positive, ART-treated adults (on ART for < 24 months) (n = 500)

Visit 1	Visit 2 (4–8 weeks after Visit 1)
– Screening, informed consent – HIV testing (HIV-negative participants only) – Blood pressure measurement – Diabetes screening^a^ – Enrollment (if meet eligibility criteria) – Participant to provide urine specimen at study clinic on day of visit (for 1st uACR and for urine albumin-to-protein ratio (uAPR) (if HIV-positive))	– Participant to provide urine specimen at study clinic on day of visit (for 2nd uACR) – Specimen collection (~ 6 tubes; ~ 30 mL total) i) *Genotyping* (Two DBS cards) ii) *Serum creatinine* (3 mL gold top tube) iii) *HBV*^*b*^* and HCV testing*^c^ (Two 3.5 mL gold top tubes) iv) *CMV testing*^d^ (One 3.5 mL gold top tube) v) *Additional specimens to store* (Two urine aliquots: Two 3 mL EDTA tubes; toenail/hair samples from consenting patients)

^a^Screen for diabetes (if symptomatic, e.g., polyuria, polydipsia, weight loss), perform fasting/random glucose test (point-of-care device) and if ≥ 6.1 mmol/L (110 mg/dL), then patient has possible diabetes, and is referred to medical provider/clinic for further evaluation

^b^Screen initially with hepatitis B surface antigen, and if positive, perform hepatitis B e Ag and hepatitis B DNA (viral load)

^c^Screen initially with hepatitis C antibody (due to anticipated low prevalence (< 1%), we will test a random sample of 200 HIV-positive adults and perform additional screening (stored samples) only if prevalence > 2%)

^d^Screen for Cytomegalovirus (CMV) using IgG antibody tests

Visit specifics are outlined in Table 1 (see above) for the newly enrolled 1250 study participants (500 HIV-positive adults on ART < 24 months plus the age- and sex-matched 750 HIV-negative adults) and in Table 2 (see below) for the 2,000 R3 participants that will be called back. Cross-sectional study visits will be completed by 1250 total participants, including 500 HIV-positive, ART-treated adults (18–69 years of age) on ART for < 24 months, plus 750 age- and sex-matched HIV-negative adults (Fig. 1). We will measure urinary albumin and creatinine levels to calculate a mean (two-sample) uACR. In the 500 HIV-positive adults, we will also measure urine protein (once at Visit 1) to perform a urine albumin-to-protein ratio (uAPR). In addition, we will call back R3 participants who completed screening but were not enrolled in the randomized trial for additional measurements. We anticipate obtaining these additional measurements from ~ 2000 R3 participants (conservatively assuming 90% re-consent). In participants called back from R3, we will obtain one uACR measurement (to confirm their current albuminuria status), one uAPR measurement (to evaluate the potential impact of current/prior TDF exposure), and serum creatinine. We will leverage archived specimens for HBV and CMV serology testing. HCV antibody testing will be performed if we identify a higher-than-expected prevalence in a random sample of 200 PWH.

**Table 2 Tab2:** Procedures for one time cross-sectional study visit for the HIV-positive, ART-treated adults that participated in the Renal Risk Reduction (R3) study and now called back (n = 2,000)

Visit 1	
-Screening, informed consent -Blood pressure measurement -Diabetes screening^a^ -Enrollment (if meet eligibility criteria) -Participant to provide urine specimen at study clinic on day of visit (for uACR and uAPR)	-Participant to provide urine specimen at study clinic on day of visit (for one-time uACR and uAPR) **Specimen collection** (~ 3 tubes; ~ 15 mLs total) i) *Serum creatinine* (3 mL gold top tube) ii) *HBV*^*b*^* and HCV testing*^c^ (leverage existing stored plasma aliquots) iii) *CMV testing*^d^ (leverage existing stored plasma aliquots) iv) *Additional specimens to store* (Two urine aliquots: Two 3 mL EDTA tubes; toenail/hair samples from consenting patients)

^a^Screen for diabetes (if symptomatic, e.g., polyuria, polydipsia, weight loss), perform fasting/random glucose test (point-of-

care device) and if ≥ 6.1 mmol/L (110 mg/dL), then patient has possible diabetes, and is referred to medical

provider/clinic for further evaluation

^b^Screen initially with hepatitis B surface antigen, and if positive, perform hepatitis B e Ag and hepatitis B DNA (viral load)

^c^Screen initially with hepatitis C antibody (due to anticipated low prevalence (< 1%), we will test a random sample of 200

HIV-positive adults and perform additional screening (stored samples) only if prevalence > 2%)

^d^Screen for Cytomegalovirus (CMV) using IgG antibody tests

##### Data collection and privacy considerations

Following enrollment, study participants will be assigned unique study identification numbers for deidentified collection of study data elements. Study visits with trained personnel will be held in private interview rooms located at AKTH. We will use REDCap for standardized, HIPAA-compliant, secure data collection using case report forms (CRFs).

#### Study measures

##### Urine albumin-to-creatinine ratio (uACR)

*In* the Aim 1 cross-sectional arm, we will determine an average uACR (based on 2 uACR measurement values obtained 4–8 weeks apart) for the 500 newly enrolled HIV-positive, ART-treated adults (on ART < 24 months) plus the 750 age- and sex-matched HIV-negative controls. We will obtain one confirmatory uACR from the 2000 HIV-positive, ART-treated adults that we will call back from the R3 Study; all these participants have two uACR measurements from the R3 screening phase.

##### Urine albumin-to-protein ratio (uAPR)

As a rough estimate of glomerular vs. tubular injury). In the Aim 1 cross-sectional arm, we will obtain one uAPR from all HIV-positive ART-treated adults (including the 500 newly enrolled HIV-positive adults [on ART < 24 months] plus the 2000 ART-experienced PWH who we call back from the R3 Study.

##### Kidney function

(Estimated glomerular filtration rate (eGFR) measurement (serum) (i.e., creatinine); In the Aim 1 cross-sectional arm, we will obtain one serum creatinine (SCr) measurement from each participant.

##### Hepatitis B and C infection status

Hepatitis B infection status to be ascertained via serum hepatitis B surface antigen testing, with hepatitis C infection status to be ascertained via serum hepatitis C antibody testing.

##### Cytomegalovirus (CMV)

Infection status. Ascertained via serum CMV IgG antibody (Ab) testing.

##### Hypertension

Study participant’s blood pressure will be classified using current Joint National Commission (JNC) 8 guidelines; namely: *Normal*: Less than 120/80 mm Hg; *Elevated*: Systolic between 120–129 and diastolic less than 80; *Stage 1*: Systolic between 130–139 or diastolic between 80–89; and *Stage 2*: Systolic at least 140 or diastolic at least 90 mm Hg.

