All information linking participants to personal identifiers will be destroyed once study follow-up and data analysis are completed. Individual participant data to be collected and maintained by de-identified study code include age, ethnicity, sex, occupation, weight, BMI, comorbid medical conditions (hypertension, diabetes, opportunistic infections, syphilis, cancer, cardiovascular disease, and other conditions of potential relevance to study outcomes), current ART regimen (for HIV-positive participants), and concomitant medications. Data on prior and current use of TDF, indinavir, and ritonavir-boosted protease inhibitors will be collected from HIV-positive participants and from review of the medical chart.

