#### Power calculations for interaction effects

We will examine whether the association between risk factors and albuminuria differs between HIV-positive and HIV-negative participants. Table 5 illustrates the power for detecting interaction effects based on hypertension. From preliminary R3 data, 12.7% of our study participants had Stage 1 or 2 hypertension (JNC-7 classification). Overall, 47% of HIV-positive adults with hypertension had albuminuria, and 39% of HIV-positive adults without hypertension had albuminuria, for a relative risk of 1.22. If the prevalence of hypertension is ~ 10% among our HIV-negative participants, then Table 5 shows the relative risks among HIV-negative individuals for which we anticipate having ~ 80% power to detect based on varying prevalence of albuminuria. For example, with 750 HIV-negative adults and a true prevalence of albuminuria of 0.25 among HIV-negative adults who do not have hypertension, we have 80% power to detect a difference of relative risks for hypertension of 1.22 vs. 2.0 between HIV-positive and HIV-negative participants, respectively (Bold emphasis row, Table 5).

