#### Statistical analysis plan

We will fit regression models based on categorized (i.e., logistic regression) and continuous (i.e., linear regression after log_10_ transformation and/or semiparametric cumulative probability models that empirically estimate the transformation) uACR levels [82]. HIV status is the primary exposure variable. We will perform additional analyses to investigate the interaction between HIV status and individual risk factors, including hypertension and co-infection (HBV and CMV), to determine whether associations differ based on HIV status (e.g., whether the impact of comorbidities on microalbuminuria is greater among PWH). Regression models will be adjusted for potential confounders, including age, ethnicity, smoking status, and BMI. Primary analyses will control for sex and will be repeated among men and women, separately, to investigate potential differences by sex. For the analyses limited to PWH, viral load (detectable/undetectable) will be included in models as a potential confounder. Missing data will be multiply imputed using standard techniques. Continuous covariates will be expanded using restricted cubic splines with three knots to avoid linearity assumptions. Additional analyses will be performed in the subset of HIV-positive adults to assess the association between HIV-specific factors (e.g., TDF exposure, duration on ART, detectable viral load, and CD4 cell count) on albuminuria/uACR (Additional file 1 and Additional file 2).

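### Aim 1 classes hypertension from measured blood pressure alone and states no handling of ACE inhibitor or ARB users, and Table 5 takes its inputs from a differently named classification

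*Protocol article*

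**What the plan says.** All references are to the protocol article.

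- **Classification.** Specific aim 1, Study measures, *Hypertension*: the participant's "blood pressure will be classified using current Joint National Commission (JNC) 8 guidelines". The four bands depend only on the reading; Stage 1, for example, is "Systolic between 130–139 or diastolic between 80–89". The Aim 1 *Study outcomes* list these same bands, by HIV status, as prevalence outcomes.
- **Aim 1 eligibility.** The exclusions are pregnancy and "Known congenital kidney disease or autoimmune disease (e.g., systemic lupus erythematosus) that can cause albuminuria". Antihypertensive treatment is not among them.
- **Aim 2 eligibility.** Under *Exclusion criteria*, people taking ACE inhibitors or ARBs are excluded, and the stated reason is that the drugs may suppress albuminuria.
- **Aim 1 models.** "Regression models will be adjusted for potential confounders, including age, ethnicity, smoking status, and BMI". Sex is also controlled for, and an interaction of HIV status with hypertension is planned.
- **Data collected.** The individual data include "comorbid medical conditions (hypertension, diabetes, opportunistic infections" and others, and "current ART regimen (for HIV-positive participants), and concomitant medications".
- **Power for the interaction.** "12.7% of our study participants had Stage 1 or 2 hypertension (JNC-7 classification"). Albuminuria was present in 47% of HIV-positive adults with hypertension and 39% of those without. About 10% of HIV-negative participants are assumed hypertensive. The bold row of Table 5 gives 80% power for relative risks of 1.22 against 2.0.

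**The concern.** Hypertension matters in several places. It is part of the overarching hypothesis, an Aim 1 prevalence outcome, and the only risk factor for which interaction power is given. Under the stated rule, a known hypertensive on effective treatment is classed Normal or Elevated. Two things follow. The prevalence comparison counts only part of the condition, by an amount that depends on how many people in each group are treated and controlled. The interaction analysis also loses true cases, of whom only about 75 are expected among HIV-negative participants.

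The treatment itself raises a separate matter. The plan recognises in Aim 2 that ACE inhibitors and ARBs can lower the outcome, but gives them no role in Aim 1. HIV-negative participants come from the General Outpatient Department and HIV-positive participants from the Virology Centre, so equal use cannot be presumed. Use that differs by HIV status would bias the primary HIV contrast.

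Finally, the prevalence and risks behind Table 5 belong to a classification with a different name from the one Aim 1 will apply, so the stated power may not describe the planned analysis.

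**Working it through.** **1. Reproducing Table 5, bold row.** Inputs from the power section: 3000 HIV-positive, 12.7% hypertensive, albuminuria 0.47 vs 0.39; 750 HIV-negative, 10% hypertensive, albuminuria 0.50 vs 0.25. A two-sided alpha of 0.05 is stated for Table 3 and assumed here. Cell sizes are 381, 2619, 75 and 675. The test is a Wald test of the interaction on the log-odds scale, matching the planned logistic model.

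- Interaction = [logit(0.50) − logit(0.25)] − [logit(0.47) − logit(0.39)] = 1.099 − 0.327 = 0.771.
- Variance = Σ 1/[n·p·(1−p)] = 1/(381×0.2491) + 1/(2619×0.2379) + 1/(75×0.25) + 1/(675×0.1875) = 0.0105 + 0.0016 + 0.0533 + 0.0079 = 0.0734; SE = 0.271.
- Power = Φ(0.771/0.271 − 1.96) = **0.813** (0.800 with 2500 HIV-positive). The stated figure is 80%.

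The arithmetic is sound for its inputs. (47/39 is 1.205, printed as 1.22; this is immaterial.)

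**2. Effect on the prevalence comparison.** If a share t of hypertensives in a group is controlled on treatment, observed prevalence = true prevalence × (1 − t). The observed prevalence ratio is therefore the true ratio × (1 − t for HIV-positive)/(1 − t for HIV-negative). With assumed shares of 10% and 30%, the factor is 0.9/0.7 = 1.29 one way round and 0.7/0.9 = 0.78 the other. The document gives neither share, so the direction is open.

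**3. Effect on the interaction (assumption-based illustration).** Suppose Table 5's prevalences were of true hypertension and a share t in both groups moved to non-hypertensive:

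| t (assumed) | Power | HIV-negative RR if treatment does not lower albuminuria | RR if treatment halves it |
|---|---|---|---|
| 0 | 0.81 | 2.00 | 2.00 |
| 10% | 0.77 | 1.98 | 2.00 |
| 20% | 0.71 | 1.96 | 2.00 |
| 30% | 0.65 | 1.94 | 2.00 |
| 50% | 0.50 | 1.90 | 2.00 |

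At t = 50%, for example, the reference risk is (0.90×0.25 + 0.05×0.50)/0.95 = 0.263 and the RR is 0.50/0.263 = 1.90. If treatment halves the risk it is (0.90×0.25 + 0.05×0.25)/0.95 = 0.25 and the RR is 2.0. The relative risk hardly moves; the loss in this illustration comes from having fewer hypertensives.

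**4. Effect of changing the classification (illustration).** The document does not give prevalence under the Aim 1 bands. With assumed prevalences (HIV-positive/HIV-negative) of 20%/16%, 30%/25% and 40%/35%:

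- risks unchanged: power 0.93, 0.98, 0.99;
- added cases carrying 40%/30% albuminuria: power 0.72, 0.62, 0.54.

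Power could rise or fall.

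**5. ACE inhibitor or ARB use and the HIV contrast (illustration).** Aim 1 has about 90% power for 0.400 vs 0.336, a difference of 6.4 points. If a quarter to a half of the assumed 10% hypertensive HIV-negatives were users (2.5% to 5%) and treatment lowered their albuminuria by 10 to 20 points, control prevalence would shift by 0.025×10 = 0.25 to 0.05×20 = 1.0 points. That is 4% to 16% of 6.4, before any offset from use among HIV-positive participants. The 10% is not a ceiling on use, because people controlled below the cut-off may lie outside it.

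**The case against.** The strongest reply is that the section on hypertension says how pressure readings are classified, not that diagnosis or treatment will be disregarded. Both are recorded, the confounder list is open-ended, and derivation rules can sit in an analysis plan that is not shown. The aims may also differ deliberately, since Aim 1 describes adults in routine care while Aim 2 needs people at risk of incident albuminuria. This stands in part: adjustment is not ruled out, and the plan does not lack the data. But the document states one rule for hypertension, its outcomes use that rule, and the rule puts controlled cases among the non-hypertensive. Nor does it reconcile its Aim 2 reasoning with Aim 1.

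Stronger readings are tempting and are not supported.

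- A reader might infer that treated cases pull the hypertension effect materially towards the null. The RR falls only from 2.0 to 1.90 with half of the cases moved, and not at all if treatment halves their albuminuria.
- A reader might infer that power really falls to 50%. Yet 12.7% is a prevalence of staged pressure, so controlled people are probably outside it already, and removing more would count the loss twice.
- A reader might assume 10–20% use among HIV-negatives, giving a shift of 1–4 points (16–63% of 6.4). That sets use at or above the assumed hypertension prevalence and assigns none to HIV-positive participants, although only differential use biases the contrast.
- Hypothesis (a) reads "Participants with hypertension (controlling for age and stage of hypertension) will have significantly higher rates of albuminuria", which seems to condition on the exposure. This is a wording matter: the Aim 2 analysis plan fits HIV status, hypertension and their interaction with no stated stage term.

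**Conclusion.** The point holds in a limited form. Aim 1's rule misclassifies diagnosed participants who are controlled on treatment. It thereby understates hypertension prevalence in each HIV group and removes true cases from the interaction. Retaining ACE inhibitor and ARB users in Aim 1 without stated handling is inconsistent with the reason given for excluding them from Aim 2. The sections on hypertension and on interaction power name different classifications. The document does not give the JNC-7 cut-offs, so the mismatch is shown by name only.

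No effect size can be given. The document reports neither the share treated and controlled, nor drug use by HIV status, nor prevalence under the Aim 1 bands. The figures in steps 2 to 5 rest on assumed inputs and show only that the effect could be small or appreciable, and that its direction on power and on the HIV contrast is not determined. The change is worth making because it is cheap and concerns a lead hypothesis.

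**What to change.** 1. For analysis, define hypertension as elevated measured pressure, documented diagnosis or current antihypertensive use. Keep pressure stage as a descriptive ordered category.
2. Repeat the primary HIV comparison excluding ACE inhibitor and ARB users, as a sensitivity analysis. Do not add use as a covariate to the primary model: use follows from hypertension and possibly from albuminuria, so adjusting for it in cross-sectional data could introduce bias.
3. Reconcile the classification named in the *Hypertension* section with the one behind the interaction power, and recompute Table 5 with prevalence and albuminuria risks under the agreed definition.

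The cost is wording, one extra analysis and a recalculation, with no new data collection. There are two drawbacks. Treated, controlled cases have no meaningful pressure stage, and excluding ACE inhibitor and ARB users selectively removes hypertensives, so the sensitivity analysis should be read with that in mind.
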